#### Recruitment and Consent Procedures

Patients will be recruited at diagnosis, after imaging or flexible cystoscopy but before endoscopic resection. Eligible patients will be identified by the clinician investigators and their teams at participating centers, ensuring adequate representation of patients in the 3 risk groups (see Textbox 1) [6]. Patients who meet eligibility criteria will be approached in person and informed about and invited to take part in the study. Consent procedures are similar to field test 1, that is, using patient information sheet and consent form for field test 2.

#### Data Collection/Assessment

##### Registration and Baseline Data

Registration data will be collected as done for field test 1. Baseline questionnaires will be completed before endoscopic resection (Table 2).

##### Follow-Up Data Collection

Participants will complete follow-up questionnaire packs at scheduled follow-up time points (see Table 2). The clinician or specialist nurse at participating centers will be responsible for sending follow-up questionnaires, emails, and reminders to participants. Participants will either be posted a hard-copy questionnaire pack or emailed a link to their follow-up questionnaires, depending on their preference. Participants who complete the Web-based questionnaire pack will be given an option to provide their email address to receive automatic reminders from the REDCap system at follow-up time points. Participants will be advised that email addresses are stored within the REDCap system and used solely for the purpose of sending reminders. REDCap is a secure Web app that runs on the University of Sydney’s servers, ensuring that data stay within the Sydney University data center. The provision of an email address for reminders is entirely voluntary, and participants will be free to change their mind at any point, after which any email address provided will be removed from the REDCap system.

##### PRO Assessment Time Points

Prospective assessment of newly diagnosed patients before and after treatment is required for the responsiveness analysis. It is expected that the NMIBC-SI will detect changes in symptoms due to specific treatments. As risk profile determines treatment schedule, the corresponding schedules of prospective assessments are indicated in Table 2. These time points will also provide PRO data to compare between treatment and risk groups and over time, addressing our clinical aims (see Aims and Objectives section).

In addition to the planned assessments (Table 2), a minimum of 25 participants sampled from each of the 3 risk groups will complete an additional NMIBC-SI 3 to 7 days after the T3 administration to evaluate test-retest reliability. The length of the test-retest interval must be short enough to ensure that clinical change in the NMIBC status is unlikely to occur but sufficiently long to ensure that respondents do not recall their responses from the first assessment. A short test-retest interval is necessary to ensure that stability per se is being evaluated, rather than clinical change during the test-retest interval, which will underestimate the NMIBC-SI’s reliability.

Participants will be sent a hard copy or link to the questionnaires 2 weeks before their scheduled follow-up time point. Up to 2 email or telephone reminders to complete follow-up questionnaires will be made if questionnaires are not completed by the follow-up date. The clinician or specialist nurse at participating centers will be responsible for sending follow-up questionnaires, emails, and reminders to participants unless participants who complete the Web-based questionnaires have provided their email address to receive automatic reminders directly from REDCap. The assessment time windows are indicated in Table 2.

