**3. Reliability**						
	3.1 Internal consistency			The extent to which items comprising a scale measure the same construct (eg, homogeneity of the scale); assessed by Cronbach alpha and item-total correlations	Cronbach alpha for summary scores ≥.70 and item-total correlations ≥.30	
	3.2 Test-retest reliability (field test 2 only)			The stability of a measuring instrument; assessed by administering the instrument to respondents on two different occasions and examining the correlation between test and retest scores	Test-retest reliability and intraclass correlations for summary scores ≥.70	

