		**Analyses against external criteria**				
			Convergent validity	Evidence that the scale is correlated with other measures of the same or similar constructs; assessed on the basis of correlations between the measure and other similar measures	Correlations are expected to vary according to the degree of similarity between the constructs that are being measured by each instrument. Specific hypotheses are formulated and predictions tested on the basis of correlations	
			Discriminant validity	Evidence that the scale is not correlated with measures of different constructs; assessed on the basis of correlations with measures of different constructs	Low correlations between the instrument and measures of different constructs	
			Known groups differences	The ability of a scale to differentiate known groups; assessed by comparing scores for subgroups that are expected to differ on the construct being measured	Significant differences between known groups or difference of expected magnitude	
5. Responsiveness				The ability of a scale to detect clinically significant change following treatment of known efficacy; assessed by examining within-person change scores before and after treatment and calculating an effect size statistic (mean change score divided by standard deviation of pretreatment scores)	Moderate to large effect sizes (small 0.2, moderate 0.5, and large 0.8 or higher)	

**Table 2 table2:** Patient-reported outcome assessment schedule.

Risk group	Assessed within 3 months before tumor resection	Assessed within 4 to 10 days after the tumor resection	Assessed within 1 month after the end of induction intravesical therapy^a^	Assessed within 1 month before the 1-year cystoscopy (or at early cessation due to adverse events^b^)
High	T1	T2	T3	T4
Intermediate	T1	T2	T3	T4
Low	T1	T2	T3^c^	T4
~n	225	225	225	225

^a^A minimum of 25 participants from each risk group will be asked to complete an additional questionnaire pack 3 to 7 days after T3.

^b^Preferably before cystoscopy.

^c^For the low-risk group, T3 will be 8 weeks after resection.

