#### Analyses and Statistical Considerations

Analyses will evaluate the measurement properties of the final version of the NMIBC-SI, using psychometric tests described for field test 1 (Table 1). Additional tests for reliability (test-retest: correlations for summary scores ≥.70), clinical validity (in terms of sensitivity to groups known to differ clinically and responsiveness to clinically meaningful change over time [37]), and estimation of minimal important difference (interpretability) [39] will be undertaken. Evaluation of subscales will be determined by factor analysis and against external criteria (between-group validity: convergent, discriminant, and known group differences validity). To evaluate convergent and discriminant validity, we will compare NMIBC-SI scales with the scales within the EORTC QLQ-C30 and QLQ-NMIBC24 measures. NMIBC-SI scores for patients by risk and treatment groups will be compared to evaluate known group differences. Risk groups are defined as low, intermediate, and high (see Textbox 1) [6]. Treatment groups are defined as follows: (1) cystoscopy alone or TURBT, (2) course of intravesical chemotherapy, and (3) course of intravesical BCG. We hypothesize that low-risk patients will have lower levels of treatment-related problems at follow-up time points compared with high-risk patients, who have more intensive treatments. Factor analysis, together with the results of other item-level analyses described in Table 1, will be used to investigate hypothesized subscales.

Analyses of the clinical aims will include: (1) evaluation of PRO changes over time, from diagnosis to peak treatment and at 1 year; (2) comparison of PROs between the 3 risk groups at each time point; and (3) head-to-head comparison of the relative discriminatory ability of the NMIBC-SI and the EORTC QLQ-NMIBC24. The pretumor resection assessment (T1) will be at diagnosis and is considered our baseline assessment. Patients are not expected to have any treatment-related problems at this point. The subsequent 3 time points (Table 2) are intended to capture short-term, intermediate, and long-term levels of problems, and each will be compared with baseline (T1).

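### The only retest follows T3, when side effects of induction may still be resolving; no item identifies stable patients, and the 0.70 criterion is worded in two ways

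*Protocol article*

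**What the plan says.** The protocol article, Field Test 2, PRO Assessment Time Points, provides for one retest: at least 25 patients per risk group "will complete an additional NMIBC-SI 3 to 7 days after the T3 administration to evaluate test-retest reliability". Table 2 places T3 as follows: "Assessed within 1 month after the end of induction intravesical therapy" for the high- and intermediate-risk groups, with the footnote "For the low-risk group, T3 will be 8 weeks after resection".

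The same section explains the interval. It should be too short for a change in disease status to be likely, and long enough that earlier answers are forgotten. It adds that clinical change in the interval would make reliability look lower than it is.

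The statistic is described in three places:

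- Table 1, row 3.2, definition: "examining the correlation between test and retest scores".
- Table 1, row 3.2, criterion: test-retest reliability and intraclass correlations of at least 0.70 for summary scores.
- Field Test 2, Analyses and Statistical Considerations: "test-retest: correlations for summary scores ≥.70".

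The Questionnaire Booklet section lists three instruments in the pack: the NMIBC-SI, the QLQ-C30 and the QLQ-NMIBC24. None is described as asking the patient to rate change since the last questionnaire. The retest is an additional NMIBC-SI in PRO Assessment Time Points but an additional questionnaire pack in the first footnote to Table 2.

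**The concern.** A test-retest study needs patients whose true score does not move between the two occasions. The stated safeguard concerns disease status, which is indeed unlikely to alter in a week. The index, however, measures symptoms and side effects, and the protocol expects it to pick up symptom changes caused by particular treatments. The Introduction also notes that BCG can have marked local and systemic effects. In the two higher-risk groups, then, an instrument built to register treatment symptoms is tested for stability when those symptoms may be receding.

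At stake is the verdict on a stated psychometric aim. The article criticises the existing EORTC bladder module for lacking test-retest evidence. If the new index fell below 0.70, nobody could tell measurement error from recovery. The loose wording of the criterion adds a second ambiguity, because a product-moment correlation ignores a common shift in scores and an agreement ICC does not.

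**Working it through.** **The plan's own figures.** The documents give no expected reliability, no expected change after T3 and no precision target for the retest. The sample-size rule reproduces (30 items × 5 = 150; 30 × 10 = 300; midpoint 225), but it does not bear on this point, because only the retest subsample counts. Its minimum is 3 × 25 = 75.

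**Inputs.** From the documents: n = 75 and the 0.70 threshold. Assumed: true reliability R = 0.80 (score variance at T3 set to 1), a mean change of d SD between test and retest, and a between-patient SD of change of τ, independent of the T3 score.

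**Formulas.** The covariance of the two scores is R, and their variances are 1 and 1 + τ². Hence

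- product-moment correlation = R / √(1 + τ²);
- absolute-agreement ICC = R / (1 + τ²/2 + d²/2).

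**Expected values and simulated chance of reaching 0.70** (n = 75, 3,000 replicates, the same change in all three groups):

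| d, τ | ICC | Correlation | ICC reaches 0.70 | Correlation reaches 0.70 |
|---|---|---|---|---|
| 0, 0 | 0.80 | 0.80 | 98% | 98% |
| 0.2, 0.3 | 0.8/1.065 = 0.75 | 0.8/√1.09 = 0.77 | 83% | 90% |
| 0.3, 0.4 | 0.8/1.125 = 0.71 | 0.8/√1.16 = 0.74 | 59% | 80% |
| 0.5, 0.5 | 0.8/1.25 = 0.64 | 0.8/√1.25 = 0.72 | 14% | 62% |

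A repeat with 6,000 replicates gave 84% and 57% for the ICC in the second and third rows, so these rates are good to about two percentage points.

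**Change in the two higher-risk groups only.** With d = 0.5 and τ = 0.5 there and none in the low-risk third, a separate run of 4,000 replicates gave 39% for the ICC and 67% for the correlation. With the same change in all groups, that run gave 15% and 63%.

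**Uniform shift needed to bring the expected ICC to 0.70** (τ = 0): d = √(2(R/0.70 − 1)). For R = 0.80 this is √0.286 = 0.53; for R = 0.75 it is √0.143 = 0.38.

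**How far the two statistics can part.** With R = 0.80, d = 0.6 and τ = 0, the correlation stays at 0.80 and reaches 0.70 in 98% of samples. The ICC is 0.8/1.18 = 0.68 and does so in 33%.

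**Precision.** An observed 0.70 has a 95% CI of about 0.56 to 0.80 at n = 75, and 0.42 to 0.86 in one risk group of 25.

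**The case against.** Several points on the other side are sound.

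- A reader might infer that the plan regards T3 as the height of treatment, since the clinical analyses run "from diagnosis to peak treatment and at 1 year". The documents do not tie that phrase to T3. The same section describes the three follow-up points as short-term, intermediate and long-term, and T3 may fall as late as a month after induction ends. The concern should rest on the Table 2 window alone.
- Low-risk patients, a third of the minimum retest sample, are retested 8 weeks after resection. The recovery argument hardly applies to them.
- A reader might also infer that the verdict could err in either direction. The calculations do not show this: every scenario starts from a reliable index (R = 0.80). If the shift is real recovery, a correlation that ignores it is not inflated by it. It would overstate agreement only if the shift were measurement drift and the correlation decided the verdict, and nothing in the documents points to drift.
- The size of change is unanchored. Table 1 calls 0.5 SD moderate for change from before to after treatment, so 0.5 SD within a week is an extreme case. At 0.2 SD the ICC still passes in 83% of samples.
- An ICC is a kind of correlation, and Table 1 names it, so the three wordings can be read as consistent. The choice of ICC model is ordinarily left to an analysis plan.
- If the retest is the full pack, the QLQ-C30 global health scale offers a rough stability check. It does not if the retest is the NMIBC-SI alone, and the two places disagree.

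What remains is a downward risk that the protocol itself recognises, no listed item to detect it, and a pass mark whose statistic is not stated uniformly.

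**Conclusion.** The point holds as a cheap improvement to the design. Unrecognised symptom change after T3 can only be expected to lower the agreement ICC, mainly through the high- and intermediate-risk groups. With true reliability 0.80 and 75 patients, the chance of meeting 0.70 falls from about 98% to 83% or 59% for mean changes of 0.2 or 0.3 SD (SD of change 0.3 or 0.4) in all three groups. Those changes are assumptions, and a stable low-risk third would soften the loss. Separately, the same data could meet 0.70 on a plain correlation and miss it on an agreement ICC, so the criterion needs one wording.

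**What to change.** 1. Add one global-change question to the retest form: symptoms since the last questionnaire are better, about the same, or worse.
2. Make the absolute-agreement ICC with its 95% CI, in patients who answer *about the same*, the primary reliability estimate. Report all retested patients as a sensitivity analysis.
3. Name the ICC as the single statistic for the 0.70 criterion in both columns of Table 1, row 3.2, and in the Field Test 2 analysis section.
4. Reconcile PRO Assessment Time Points with the Table 2 footnote on whether the retest is the NMIBC-SI alone or the full pack.

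The cost is one question for about 75 patients and some rewording; no assessment time point moves. The drawback is a smaller stable subset and a wider CI. Since 25 per group is a minimum, sites can offset this by inviting more of the patients already enrolled.

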#### Mode of Questionnaire Administration

Participants will be given a hard copy of the questionnaire or provided with a link to the Web-based questionnaire depending on their preference.

#### Questionnaire Booklet

A questionnaire pack containing the NMIBC-SI, EORTC QLQ-C30, and the EORTC QLQ-NMIBC24 will be self-completed by all participants via hard copy or Web.

Participants will complete the item-reduced version of the NMIBC-SI, the QLQ-C30, and the QLQ-NMIBC24 measures to assess construct validity (convergent, discriminant, and known groups; see Table 2). The guiding principle in selecting the validating measures is to include measures that will allow a comparison of NMIBC-SI subscales with measures of similar constructs (convergent validity) and with measures of different constructs (discriminant validity), and to compare NMIBC-SI scores in clinically defined known groups whose HRQoL would be expected to differ.

The QLQ-C30 [38] is a core questionnaire for evaluating the HRQoL of patients participating in cancer clinical trials. It is a 30-item questionnaire with 9 multi-item subscales and 6 single items. It incorporates 5 functional scales (physical, role, cognitive, emotional, and social functioning), 3 symptom scales (fatigue, pain, and nausea or vomiting), and a global health status or HRQoL scale. The single items assess dyspnea, appetite loss, sleep disturbance, constipation, diarrhea, and perceived financial impact of disease and treatment. Ratings for each item range from 1 (not at all) to 4 (very much). The QLQ-C30 is designed to be used across cancer populations and takes about 11 min to complete [38].

The QLQ-NMIBC24 [20] is a 24-item questionnaire for evaluating the HRQoL of patients with superficial (nonmuscle invasive) bladder cancer. The questionnaire is designed to supplement the QLQ-C30 and incorporates 6 multi-item scales and 5 single items. Ratings for each item range from 1 (not at all) to 4 (very much). The scales cover urinary symptoms, malaise, worries about the future, bloating and flatulence, sexual function, and male sexual problems. The single items assess intravesical treatment issues, sexual intimacy, sexual enjoyment, risk of contaminating partner, and female sexual problems.

All measures will be administered in the same order. It is anticipated that completion of questionnaire packs may take up to 20 min.

#### Analyses and Statistical Considerations

Analyses will evaluate the measurement properties of the final version of the NMIBC-SI, using psychometric tests described for field test 1 (Table 1). Additional tests for reliability (test-retest: correlations for summary scores ≥.70), clinical validity (in terms of sensitivity to groups known to differ clinically and responsiveness to clinically meaningful change over time [37]), and estimation of minimal important difference (interpretability) [39] will be undertaken. Evaluation of subscales will be determined by factor analysis and against external criteria (between-group validity: convergent, discriminant, and known group differences validity). To evaluate convergent and discriminant validity, we will compare NMIBC-SI scales with the scales within the EORTC QLQ-C30 and QLQ-NMIBC24 measures. NMIBC-SI scores for patients by risk and treatment groups will be compared to evaluate known group differences. Risk groups are defined as low, intermediate, and high (see Textbox 1) [6]. Treatment groups are defined as follows: (1) cystoscopy alone or TURBT, (2) course of intravesical chemotherapy, and (3) course of intravesical BCG. We hypothesize that low-risk patients will have lower levels of treatment-related problems at follow-up time points compared with high-risk patients, who have more intensive treatments. Factor analysis, together with the results of other item-level analyses described in Table 1, will be used to investigate hypothesized subscales.

Analyses of the clinical aims will include: (1) evaluation of PRO changes over time, from diagnosis to peak treatment and at 1 year; (2) comparison of PROs between the 3 risk groups at each time point; and (3) head-to-head comparison of the relative discriminatory ability of the NMIBC-SI and the EORTC QLQ-NMIBC24. The pretumor resection assessment (T1) will be at diagnosis and is considered our baseline assessment. Patients are not expected to have any treatment-related problems at this point. The subsequent 3 time points (Table 2) are intended to capture short-term, intermediate, and long-term levels of problems, and each will be compared with baseline (T1).

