#### Psychometric Aims

To evaluate the feasibility and acceptability of the NMIBC-SI; produce a shorter version, if appropriate, by selecting items that perform best against robust psychometric criteria; examine the legitimacy of summing items into scales; identify legitimate scales and subscales; and test scaling assumptions and scale performance in a large-scale Australian sample (field test 1).To psychometrically evaluate the measurement properties of the final version SI, testing for reliability, clinical validity (sensitivity to differences between patient groups and responsiveness to clinically important change), and interpretability of the final version NMIBC-SI in a new large-scale international sample (field test 2).To conduct a head-to-head comparison of the new NMIBC-SI with the EORTC bladder cancer module, QLQ-NMIBC24.

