The evaluation of the NMIBC-SI is phase 2 of this project. It will be undertaken in 2 parts: preliminary field test 1 (item reduction) and final field test 2 (psychometric properties). The preliminary field test will identify any items with poor psychometric performance for possible elimination. The final field test will be undertaken to evaluate the item-reduced version of the NMIBC-SI for reliability, validity, and responsiveness. Gold standard psychometric methods will be used [11,22,23].

### Phase 2: Field Test 1

The psychometric properties of the NMIBC-SI will be evaluated in 2 field tests, including a preliminary field test (item reduction) to identify items with poor psychometric properties for possible elimination and to identify subscales, and a final field test (psychometric evaluation) to evaluate the reliability and validity of the item-reduced version of the NMIBC-SI. The overall strategy and methods for the psychometric evaluation are based on the methods used to develop and validate PROMs in several other areas of medicine and surgery [24-26].

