**Figure 1 figure1:**
[figure not shown]
Development and evaluation of the symptom index for individuals with nonmuscle invasive bladder cancer.

Results of the item reduction analyses will be used to develop a shorter version of NMIBC-SI for final psychometric field testing.

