### Phase 2: Field Test 2—Evaluation of Reliability and Clinical Validity

#### Design for Field Test 2

The purpose of the final field test 2 is to assess the reliability and clinical validity (sensitivity to differences between patient groups and responsiveness to clinically important change) and interpretability of the final version NMIBC-SI in a new large-scale international sample. This phase will be conducted using a prospective longitudinal study design. The outcome will be a patient-reported NMIBC-SI that is reliable and clinically valid, with NMIBC-specific content that complements the more generic HRQoL content of the EORTC QLQ-C30.

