#### Sample Size

Approximately 225 patients newly diagnosed with NMIBC will be required to provide sufficient subjects for statistical assessment of test-retest reliability [34,35] and clinical validity in terms of both sensitivity to differences between patient groups [36] and responsiveness to clinically important change [37]. See section on Sample Size for Field Test 1 for sample size justification.

**Table 1 table1:** Psychometric tests and criteria.

Property				Definition/test	Criteria for acceptability	
1. Item analysis				Identify items for possible elimination due to weak psychometric performance; assessed on the basis of (1) exploratory factor analysis with principal axis factoring and (2) item- and scale-level analyses	Exploratory factor analysis: items with a factor-loading coefficient ≥0.4 will be retained in each subscale. Applied to all items: (1) missing data <5%; (2) maximum endorsement frequencies <80% (ie, the proportion of respondents who endorse each response category), including floor or ceiling effects <80% (ie, response categories with high endorsement rates at the bottom and top ends of the scale, respectively); (3) evidence of item responsiveness as assessed by significant improvement between baseline and test of cure assessments (field test 2 only)	
2. Acceptability				The quality of data; assessed by completeness of data and score distributions	Missing data for summary scores <20%; normal distribution of endorsement frequencies across response categories (ie, absence of skew, endorsement rates between 0.20 and 0.80); and floor or ceiling effects for summary scores <10%	

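### Table 1 carries an item-elimination criterion reserved for field test 2, so the independent evaluation of the final NMIBC-SI is not protected

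*Protocol article*

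**What the plan says.** The division of labour is stated several times in the protocol article.

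- **Field test 1** is cross-sectional and reduces the items. Under Design for Preliminary Field Test 1: "Results of the item reduction analyses will be used to develop a shorter version of NMIBC-SI for final psychometric field testing".
- **Field test 2** is longitudinal. Under Overview of Project Research Design: "The final field test will be undertaken to evaluate the item-reduced version of the NMIBC-SI for reliability, validity, and responsiveness". Psychometric Aims has the same purpose: "To psychometrically evaluate the measurement properties of the final version SI". Design for Field Test 2 adds "interpretability of the final version NMIBC-SI in a new large-scale international sample". The Questionnaire Booklet section has patients complete the reduced version, and the Discussion says that the two samples do not overlap.

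The analysis section for field test 2 then says: "Analyses will evaluate the measurement properties of the final version of the NMIBC-SI, using psychometric tests described for field test 1 (Table 1"), with no row left out. Row 1 of Table 1 (Item analysis) has this purpose: "Identify items for possible elimination due to weak psychometric performance". Its third criterion reads: "evidence of item responsiveness as assessed by significant improvement between baseline and test of cure assessments (field test 2 only"). The same row names exploratory factor analysis and keeps items that load at 0.4 or above, without tying this to either field test. On subscales, the field test 2 section adds: "Factor analysis, together with the results of other item-level analyses described in Table 1, will be used to investigate hypothesized subscales". Confirmatory factor analysis appears in row 4.2, also not assigned to a field test.

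**The concern.** Field test 2 is valuable because its patients had no part in choosing the items. An elimination criterion that can operate only on those patients works against this. If it were acted on, items would be kept because they happened to change in this sample. The responsiveness of the surviving scale would then be reported from the same data, next to test-retest reliability, known-groups results, the minimal important difference and the comparison with the QLQ-NMIBC24. The article names no split sample or later sample in which a revised version could be confirmed. The index is intended as a clinical trial endpoint, so a reader needs to know exactly which version the reported properties describe.

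**Working it through.** **1. The text.** Criterion 3 compares two time points. Field test 1 has one assessment per patient, so the criterion cannot be applied there, as its own label confirms. It belongs to a row whose purpose is to find items to remove, and it becomes usable only once the version is called final. The two statements do not fit together as printed.

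**2. The plan's own figure.** Sample Size for Field Test 1 uses 5 to 10 subjects per item and 30 items: 5 × 30 = 150 and 10 × 30 = 300. The midpoint is (150 + 300)/2 = 225, or 7.5 per item. Field test 2 also has about 225 and refers back to that section. The number is not in dispute. One risk group would have 225/3 = 75 patients if the groups were equal, which is an assumption.

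**3. What acting on criterion 3 would do.** The article gives no item-level changes or correlations, so this rests on assumptions.

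- Rule modelled: an item is kept if t = mean change / (SD of change / √n) exceeds 1.96. Dropping is automatic, which is stricter than the text.
- Effect size, as in Table 1 row 5: mean change of the retained scale / SD of its baseline scores.
- Optimism: effect size in the selecting sample minus its true value, or minus the value in an independent sample of equal size.

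*Setting A:* 6 to 20 items, inter-item correlation 0.35, mean true item change 0.1 to 0.3 SD, spread 0.1 SD. Optimism is 0.007 to 0.045 with n = 225 and 0.058 to 0.162 with n = 75.

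*Setting B:* 30 items, inter-item correlation 0.3, pre/post correlation 0.5, spread 0.1 SD. Runs in which fewer than three items survived are left out.

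| n used to select | Mean true item change (SD) | Same sample | Independent sample | Optimism |
|---|---|---|---|---|
| 225 | 0.1 | 0.353 | 0.310 | 0.043 |
| 225 | 0.2 | 0.442 | 0.418 | 0.024 |
| 225 | 0.3 | 0.558 | 0.552 | 0.006 |
| 75 | 0.1 | 0.480 | 0.303 | 0.177 |
| 75 | 0.2 | 0.553 | 0.442 | 0.111 |
| 75 | 0.3 | 0.651 | 0.583 | 0.068 |

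If the mean true change is 0, the gap in setting B is 0.288 − 0.204 = 0.084 at n = 225 and 0.434 − 0.187 = 0.247 at n = 75.

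**4. Where selection takes place matters.** With inter-item correlation 0.35 and pre/post correlation 0.5, selecting items on all 225 and then reporting the effect size in a subgroup of 75 still gives only about 0.01 to 0.05. The larger figures need the selection itself to be made within about 75 patients.

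**5. Criterion 3 against the schedule.** It refers to a test of cure assessment, but Table 2 defines only T1 to T4 and none carries that name. It also asks for improvement from baseline, whereas the field test 2 analysis section expects no treatment-related problems at T1. A side-effect item that starts near zero can hardly improve. Read literally, the criterion counts against items on treatment side effects, which the index was built to capture.

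**The case against.** The strongest reply is that no sentence says items will be removed after field test 2. Table 1 speaks only of possible elimination, every passage that assigns item reduction assigns it to field test 1, and the governing verb for field test 2 is to evaluate. Running an item-level responsiveness check on a finished instrument is ordinary practice. A full protocol or analysis plan, not shown here, may fix the version explicitly.

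Much of this stands, and it rules out several stronger readings.

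- A reader might infer that the plan does eliminate items in field test 2. The documents support only that it leaves this open.
- A reader might infer that subscales are derived afresh. The wording concerns hypothesized subscales, and confirmatory factor analysis is listed, so testing a prespecified structure is at least as natural a reading. Re-derivation is possible only because the exploratory rule is not limited to field test 1.
- A reader might take a severe case as typical. With 20 items, mean change 0.2 SD and selection within 75 patients, about half of the surviving scales reach the 0.5 threshold for a moderate effect while about 3% truly do. Selection on all 225 gives about 4% against 0.4%. Nothing in the article says that items are selected within a subgroup.
- A reader might infer that the comparison with the QLQ-NMIBC24 is tilted. That comparison concerns discrimination between groups, whereas the simulations cover change within patients. No bias there has been computed.

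The reply does not remove the label on criterion 3. This is something the article states, not a detail it leaves to another document.

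**Conclusion.** The concern holds in conditional form. The article calls the field test 2 instrument final, yet gives an elimination row a criterion that only field test 2 can apply. The independence of the evaluation is therefore unprotected, which is not the same as lost. If items were dropped or subscales changed on field test 2 results, the published properties would belong to a version chosen on the same patients and never administered as such.

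Under the assumptions above, with automatic dropping and mean item changes of 0.1 to 0.3 SD, the inflation of the responsiveness effect size is about 0.01 to 0.05 for selection on the whole sample. This is small against the 0.5 threshold. It would be about 0.06 to 0.18 for selection within about 75 patients, which is not planned. Effects on reliability, known-groups results and the head-to-head comparison are not quantified. Separately, criterion 3 does not match the assessment schedule or the expected state at T1. The point is worth acting on because the correction is cheap, not because the likely whole-sample bias is large.

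**What to change.** - State that the item set, subscales and scoring from field test 1 are locked before field test 2 opens.
- State that in field test 2 all of Table 1 row 1, including criterion 3, is descriptive and leads to no elimination.
- Assign exploratory factor analysis to field test 1, and test the locked structure in field test 2 by confirmatory factor analysis.
- Report reliability, responsiveness, known-groups results, the minimal important difference and the head-to-head comparison for the locked version. Label any later change as a new version that needs its own validation.
- Reconcile criterion 3 with the schedule: tie it to named time points among T1 to T4, and resolve the conflict between requiring improvement and expecting no treatment-related problems at T1.

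This changes wording only, with no further patients or assessments. The price is that a weak item discovered in field test 2 stays in the evaluated version.
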